### 3) Number of Subjects and Rationale

This study is a prospective pilot investigator-initiated clinical trial. The results obtained from this study will be used to calculate the number of participants for future confirmatory clinical trials. A total of 100 subjects will be recruited, with 50 in the treatment group (receiving Kyung-Ok-Go) and 50 in the control group (receiving placebo).

| Institute                                       | Treatment group | Control group | Sum |
|-------------------------------------------------|-----------------|---------------|-----|
| Kyunghee University
Korean Medicine Hospital | 30              | 30            | 60  |
| Dongueui University
Korean Medicine Hospital | 20              | 20            | 40  |
| Sum                                             | 50              | 50            | 100 |

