### **11.3 Blinding, etc.**

At Visit 0, each subject will be assigned a unique screening number by the researcher. This number will begin with CVS1-01 at Kyung Hee University Korean Medicine Hospital and CVS2-01 at Dong-Eui University Korean Medicine Hospital, and will be assigned in ascending order from the smallest available number. Once assigned, the screening number will not be reused. If a subject is not treated at Visit 1 for any reason, the screening number assignment and the reason for non-treatment will be documented in the Screening Log and the case report form (CRF).

Block randomization will be employed, and the block size will not be disclosed to maintain blinding. An independent statistician will generate random numbers using STATA Version 4.2 (StataCorp LLC., Texas), and these numbers will be sent to the labeling site for the IMPs, where they will be labeled and packaged in the order of randomization. This ensures both the researcher and the subjects are blinded. The probability of allocation to the treatment or control group is 1:1.

To ensure allocation concealment, the IMPs packaged according to the random numbers generated by the independent statistician will be delivered to the trial sites. Subjects who meet the inclusion criteria, do not meet the exclusion criteria, and voluntarily consent in writing will be assigned the lowest available random number in the order of their participation. This number will be recorded in the CRF, and the IMP will be dispensed accordingly.

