## 14. Statistical Analysis Methods

### 14.1 General principles of result analysis

The primary analysis for efficacy evaluation will use the Full Analysis Set (FAS). Safety evaluations will be conducted using the Safety Set. All statistical tests will be two-sided with a significance level of 5%. For efficacy evaluation, missing data in the FAS will be handled using the Last Observation Carried Forward (LOCF) method for statistical analysis, while all other data will be analyzed as originally recorded.

**Safety Set (SS):** A group of subjects who have received the investigational medicinal product at least once and have undergone at least one safety-related follow-up.

**Full Analysis Set (FAS):** A group of subjects who, in accordance with the ITT principle, have received the investigational medicinal product and have at least one measurement of the primary efficacy variable.

For analyses other than efficacy evaluation, such as feasibility evaluation (e.g., recruitment rate, dropout rate, reasons for dropout), the recruitment rate will be calculated as the number of enrolled subjects divided by the total number of screened subjects (%). Dropout rates and

reasons will be analyzed descriptively for both the entire study and each herbal preparation group.

To compare differences between groups for efficacy variables, ANCOVA will be conducted with the assigned group as the factor and the baseline value as the covariate (two-sided  $p < 0.05$ ). If assumptions of ANCOVA (normality, homoscedasticity) are violated or outliers are observed, Ranked ANCOVA will be performed. For categorical data, frequencies and percentages will be calculated, and comparisons between groups will be made using the Chi-square test or Fisher's exact test (if expected frequency is  $\leq 5$ ). Statistical analyses will be conducted using R-software (latest version) or jamovi software (latest version).

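### The FSS ANCOVA omits hospital although 1:1 allocation is planned within each, and an undefined outlier is enough to replace it with a rank analysis that gives no FSS difference

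*Protocol*

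**What the plan says.** Four statements in the protocol bear on this point.

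- **Model (section 14.1).** For the efficacy variables, "ANCOVA will be conducted with the assigned group as the factor and the baseline value as the covariate". Hospital does not appear. Tests are two-sided at 5%.
- **Switch (section 14.1, same paragraph).** "If assumptions of ANCOVA (normality, homoscedasticity) are violated or outliers are observed, Ranked ANCOVA will be performed". No outlier definition, assumption test or cut-off is given, and nothing says that the ANCOVA on the FSS scale is kept alongside.
- **Planned numbers (section 7, 3) Number of Subjects and Rationale).** The table gives, for the first hospital, "Korean Medicine Hospital | 30 | 30 | 60" and, for the second, "Korean Medicine Hospital | 20 | 20 | 40". The columns are treatment, control and sum. The same section says that the results will serve to calculate the sample size of later confirmatory trials.
- **Randomisation (section 11.3).** "Block randomization will be employed, and the block size will not be disclosed to maintain blinding". The ratio is 1:1. Packs are labelled in randomisation order and delivered to the sites, and each participant takes the lowest available number. Screening numbers carry a hospital prefix, but the section does not say whether the randomisation list is separate for each hospital.

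**The concern.** **Site.** When arms are balanced within hospital by design, any difference between the hospitals cancels out of the treatment comparison. A model without hospital still counts that difference as residual noise, so the reported standard error exceeds the real one. If the list is not stratified, the noise is real and the standard error is honest, but precision that one model term would recover is given up.

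**Switch to ranks.** The choice of primary method depends on the outcome data through a word that the protocol does not define. Two careful analysts could therefore reach different primary methods from the same data. A rank ANCOVA returns a difference in mean ranks. It gives no adjusted difference in FSS points and no residual SD on that scale, which are the quantities needed to size the next trial.

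Both rules are written into the protocol, so this is not detail merely left to a statistical analysis plan.

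**Working it through.** **The plan's own figures.** 30 + 20 = 50 per arm and 60 + 40 = 100 in total. The table is consistent. The protocol gives no effect size, SD, power or site difference, so every site difference below is an assumption.

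**1. Omitting site, arms balanced within hospital.** Let d be the difference between hospitals, in residual SDs, after adjustment for baseline. With a 60:40 split, hospital adds 0.6 × 0.4 × d² = 0.24d² to a residual variance of 1. The reported standard error is therefore too large by a factor √(1 + 0.24d²).

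The true type I error is the chance that a correctly scaled t statistic exceeds 1.985 (the two-sided 5% point on 97 df) times this factor.

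| d | SE factor | Rejection limit | Type I error |
|---|---|---|---|
| 0 | 1.000 | 1.985 | 5.0% |
| 0.5 | √1.06 = 1.030 | 2.043 | 4.4% |
| 0.8 | √1.1536 = 1.074 | 2.132 | 3.6% |
| 1.0 | √1.24 = 1.114 | 2.210 | 2.9% |

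Simulation (6,000 runs per setting, baseline slope 0.5) agrees. Without site, the mean standard error is 0.206 at d = 0.5 and 0.224 at d = 1.0. With site it is 0.200 to 0.201 throughout, and type I error is 4.6% to 5.2%. For an assumed treatment effect of 0.5 SD, power without site is 67% (d = 0.5) and 61% (d = 1.0), against about 69% with site. The estimate is unbiased either way.

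**2. Omitting site, list not stratified.** Assume blocks of 4 on one list and interleaved recruitment at the two hospitals. Over 10,000 runs, the model without site has type I error 4.9% at d = 0.5 and 5.0% at d = 1.0. The empirical SD of the estimate matches the mean reported standard error (0.208 against 0.207, and 0.225 against 0.224). With site, the empirical SD is 0.202 in both cases. The standard error is valid here, and the loss is precision alone.

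**3. How often the outlier trigger fires when nothing is wrong.** Normal data or residuals, n = 100, 20,000 runs:

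| Rule | Trials with at least one outlier |
|---|---|
| Beyond 3 IQR | 0.2% to 0.3% |
| Absolute z > 3 | 18% to 21% |
| Beyond 1.5 IQR (boxplot) | 54% to 55% |

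The ranges cover repeated simulations and application to raw values or to residuals. Adding Shapiro-Wilk and Levene tests at 5% to the 1.5-IQR rule gives 58%. The FSS is a nine-item mean bounded at 1 and 7. On simulated bounded raw scores (assumed mean 4 to 4.5, SD 1.3), the 1.5-IQR rule fires in about 16% to 27% of trials and the z rule in 0% to 2%.

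**4. Does the switch inflate type I error?** ANCOVA was run unless the 1.5-IQR rule or Shapiro-Wilk triggered ranks (8,000 runs). Type I error was 5.4% with normal residuals and 5.3% with t residuals on 5 df. ANCOVA alone gave 5.1% and 5.3% in the same runs, so the inflation is not material.

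**The case against.** **Nothing shows that the error bars are wrong.** A reader might infer from the table that allocation is fixed 1:1 within each hospital and that the reported standard errors must therefore be wrong. The documents do not support that. The table gives planned numbers, section 11.3 never states stratification, and no site difference is given anywhere. If the hospitals do not differ after baseline adjustment, the standard error is right; if the list is not stratified, it is also right. In the remaining case it is too large, so the error is conservative. Both hospitals apply the same FSS entry threshold and questionnaire, so a gap near 1 SD would be large. All of this stands, and it makes the site half a modest matter of efficiency.

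**Within-site balance may arise anyway.** If packs are shipped to each hospital as consecutive runs and the block size is 4, then 60 and 40 are whole numbers of blocks and the table is met exactly. That is possible, but section 11.3 does not say so. The section needs clarifying; it does not show an error.

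**An outlier rule is ordinary analysis-plan content, and one choice makes the switch very rare.** This is fair as to the missing definition. It does not cure the protocol's own rule that an observed outlier changes the primary method, when reasonable definitions move the switch rate from near zero to over half on clean data.

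**The FSS data are not lost.** A reader might infer that switching destroys the FSS estimate or spoils error control. Arm means and SDs remain computable, and the two-stage type I error stays near 5%. What goes missing is the adjusted FSS difference as the output of the primary analysis.

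**Conclusion.** The point holds in two limited parts, and the rank switch is the stronger.

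- **Site.** The model omits a factor on which the protocol plans balance. The intervals are too wide only if allocation is balanced within hospital and the hospitals differ: about 3% in standard error at 0.5 SD and 11% at 1.0 SD, with type I error about 4.4% and 2.9%. Under unstratified allocation, inference is valid and the same term would buy precision. There is neither bias nor false-positive inflation in either case.
- **Rank switch.** The primary method hangs on an undefined word. The switch rate on normal data runs from about 0.2% to 55% according to the definition chosen, and is lower on bounded scores for the 1.5-IQR and z rules. The harm is an analyst-dependent method and a primary result without an adjusted FSS difference, in a pilot whose stated use is to size a confirmatory trial.

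The site figures rest on assumed values of d. The trigger rates rest on assumed outlier rules.

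**What to change.** 1. Reconcile section 7 with section 11.3 by stating that the block lists are separate for each hospital (30/30 and 20/20). If the lists are not yet built that way, this must be settled before packs are labelled.
2. In section 14.1, add hospital as a fixed factor to the primary and secondary ANCOVAs.
3. Keep the FSS-scale ANCOVA primary whatever the diagnostics show, and report the adjusted difference, its 95% CI and the residual SD.
4. Make Ranked ANCOVA a sensitivity analysis. Heteroscedasticity-robust standard errors are optional and add little with equal arms.

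The cost is one degree of freedom and a few sentences, and the model wording can be changed at any time before unblinding. The one statistical downside is slightly lower power than ranks if residuals are very heavy-tailed, which a scale bounded at 1 and 7 limits.

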#### **14.2 Demographic baseline data**

To test for statistical differences between the two groups in baseline demographic data, FSS scores, and 0-100 VAS scores for symptoms, the following steps will be taken:

Continuous data: mean, standard deviation, median, minimum, and maximum will be calculated, and comparisons will be made using the independent two-sample t-test or Wilcoxon rank-sum test.

Categorical data: frequencies and percentages will be calculated, and comparisons will be made using the Chi-square test or Fisher's exact test (if expected frequency is  $\leq 5$ ).

To ensure comparability between the two groups, the FSS score, ChFS score and subscale scores, EQ-5D-5L score, PSQI-K Global score, K-MOCA score, BDI score, DF score, DB score, DF-DB score, K-BNT-15 score, computerized neurocognitive test scores, and SPPB test scores will be calculated for each group and compared using the independent two-sample t-test or Wilcoxon rank-sum test.

#### **14.3 Analysis of efficacy variables**

##### **14.3.1 Primary efficacy variable**

FSS score after 12 weeks of intervention

##### **14.3.2 Secondary efficacy variables**

- 1) Final medication adherence
- 2) Differences in final medication adherence between groups
- 3) FSS scores at visit 2 and visit 3
- 4) ChFS scores and subscale scores at visits 2, 3, and 4
- 5) EQ-5D-5L scores at visit 4
- 6) PSQI-K Global score at visit 4
- 7) K-MOCA total and domain scores at visit 4

- 8) BDI scores at visit 4
- 9) DF score, DB score, and DF-DB score at visit 4
- 10) Computerized neurocognitive test scores at visit 4
- 11) SPPB test scores for walking speed, sit-to-stand test, balance test, and total score at visit 4
- 12) Analysis of recruitment rate, dropout rate, and reasons for dropout for feasibility evaluation
- 13) Treatment success rate in fatigue symptoms after 12 weeks of intervention compared between the treatment and control groups

#### **14.4 Analysis of safety variables**

##### **14.4.1 Adverse events**

Adverse events (AEs) are defined as any unfavorable symptoms, signs, or diseases occurring in subjects administered the investigational medicinal product. The number of subjects experiencing all AEs, adverse drug reactions (ADRs), serious adverse events (SAEs), and serious adverse drug reactions (SADRs), along with their incidence rates and 95% confidence intervals, will be presented for each group. Differences between groups will be tested using the Chi-square test or Fisher's exact test. All AEs will be coded using the Medical Dictionary for Regulatory Activities (MedDRA) and presented by system organ class (SOC) and preferred term (PT).

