### 16.2 Evaluation criteria

#### (1) Severity of adverse events

The severity of adverse events (Intensity) will be evaluated as follows:

| severity | explanation                                                                                                                                 |
|----------|---------------------------------------------------------------------------------------------------------------------------------------------|
| Mild     | Minimal interference with normal daily activities (function) and requires no special treatment.                                             |
| Moderate | Causes discomfort and interferes with normal daily activities (function). The participant can continue the trial but may require treatment. |
| Severe   | Causes significant discomfort, making normal daily activities (function) impossible, requiring treatment or hospitalization.                |

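### The only planned between-arm comparison of adverse events is a 5% significance test, which is insensitive to uncommon events with 50 per arm; a risk difference with its 95% CI should lead

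*Protocol*

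**What the plan says.** Protocol Section 14.4.1 covers four categories: all AEs, ADRs, serious AEs (SAEs) and serious ADRs (SADRs). Subject counts, "along with their incidence rates and 95% confidence intervals, will be presented for each group". The next sentence deals with the comparison: "Differences between groups will be tested using the Chi-square test" or Fisher's exact test. Events are also tabulated by MedDRA system organ class and preferred term. The Summary describes the same analysis and adds the number of events per group.

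Section 14.1 sets the level: "All statistical tests will be two-sided with a significance level of 5" per cent. For categorical data in general it uses Fisher's test when the expected frequency is 5 or less, and Chi-square otherwise. Section 14.4.1 names both tests without repeating that rule.

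On size, Section 7, item 3 says: "A total of 100 subjects will be recruited, with 50 in the treatment group", and the other 50 receive placebo. No effect size, event rate or power lies behind this. The stated rationale is that "The results obtained from this study will be used to calculate the number of participants for future confirmatory clinical trials". Evaluating safety is one of the purposes given in Section 5, item 2.

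**The concern.** A placebo-controlled safety comparison should show how much more often a reaction occurs on the herbal product than on placebo, and how large an excess the data leave open. Neither planned output does this. The per-arm intervals describe each arm separately and cannot be read as an interval for the difference. The test returns only a p-value.

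For uncommon events in a trial of this size, a non-significant p-value is the expected result even when the product does harm. The trial is meant to inform a later confirmatory study, and that study needs the size and uncertainty of any excess.

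**Working it through.** The protocol gives no power or detectable difference for AEs, so there is no stated figure to reproduce.

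**Inputs**
- 50 per arm (Section 7, item 3), allocated 1:1 (Section 11.3).
- Two-sided 0.05, and Fisher when the expected count is 5 or less, otherwise Chi-square (Section 14.1).
- Event rates: none is given. Section 27 only calls the listed risks rare. The rates below are assumptions, with placebo from 1% to 15%.
- Chi-square is taken without continuity correction, because the protocol does not mention one.

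**When each test applies.** With equal arms and *a* and *b* subjects with events, the expected count per arm is (a + b)/2. Fisher therefore applies whenever the two arms together have 10 or fewer subjects with events.

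**Power.** For true rates q (active) and p (placebo), sum over all 51 × 51 outcomes: power = Σ Bin(a; 50, q) × Bin(b; 50, p) over the pairs (a, b) whose p-value is below 0.05.

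| Active vs placebo | Protocol's rule | Fisher throughout |
|---|---|---|
| 3% vs 1% | 0% | 0% |
| 6% vs 2% | 3% | 3% |
| 10% vs 2% | 20% | 19% |
| 15% vs 5% | 31% | 24% |
| 18% vs 6% | 43% | 33% |
| 21% vs 7% | 53% | 41% |
| 24% vs 8% | 61% | 49% |
| 30% vs 10% | 73% | 64% |
| 45% vs 15% | 92% | 89% |

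Every row except 10% vs 2% is a tripling. Under the protocol's rule, power for a tripling passes 50% between placebo rates of 6% and 7%. With Fisher throughout, it does so just above 8%. If only 40 per arm were analysed (an assumption), the crossover under the protocol's rule would lie between 8% and 9%.

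**A check that needs no assumed rate: 5/50 vs 0/50.** There are 5 events in all, so Fisher applies.
- p = 2 × C(50,5)/C(100,5) = 2 × 2,118,760/75,287,520 = 0.056, not significant.
- For 6 vs 0, p = 2 × C(50,6)/C(100,6) = 0.027. Against no placebo events, 6 is therefore the smallest count that reaches significance.

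**Newcombe interval for 5/50 vs 0/50.** The Wilson limits are 4.35% to 21.36% (active) and 0% to 7.13% (placebo). The difference is 10 points.
- Lower limit: 10 − √[(10 − 4.35)² + (7.13 − 0)²] = 10 − 9.10 = +0.9 points.
- Upper limit: 10 + √[(21.36 − 10)² + (0 − 0)²] = +21.4 points.

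**A second example: 6/50 vs 2/50.** Fisher p = 0.27. The difference is 8 points, with a Newcombe interval of −3.4 to +20.2. The p-value alone does not show that an excess of 20 points remains possible.

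**The case against.** The strongest reply is that nothing here is computed wrongly. Both tests are valid for these data. Counts, incidences, per-arm intervals and MedDRA tables are all presented, so anyone can derive the risk difference. An SAP that is not shown may also add the interval. This stands in part: it rules out any claim that AEs are judged by a p-value and nothing else. It does not remove the point, because the protocol itself fixes the between-arm method, and that method is a test without an estimate.

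Three stronger readings are tempting, and the documents do not support them.
- A reader might infer that even a tripled reaction rate would usually go undetected. That fails without a base rate. Power is 73% at 30% vs 10% and 92% at 45% vs 15%, and the category of all AEs could plausibly reach such rates over 12 weeks.
- A reader might infer that p > 0.05 will be reported as equal safety. No section says so or ties any decision to this test. The risk is a foreseeable misreading.
- A reader might count the absence of severity from Section 14.4.1 as an error. Severity is graded under Section 16.2 and recorded in the case report form. A table by grade can properly be left to the SAP, so its absence is no finding.

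Fisher's test is also conservative. The 5 vs 0 interval excludes zero partly because it comes from a less conservative method. The example shows what an interval conveys and should not be taken as proof of harm.

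**Conclusion.** The point holds for uncommon events. In a 50-per-arm pilot with safety among its purposes and no sample-size calculation, a two-sided 5% test is a poor choice as the only between-arm AE comparison. Power under the protocol's rule is about 3% for 6% vs 2%, 20% for 10% vs 2% and 31% for 15% vs 5%. A tripled rate is missed more often than not only below a placebo rate of about 7%. These powers rest on assumed event rates, on all 50 per arm being in the Safety Set, and on an uncorrected Chi-square. The 5 vs 0 result (p = 0.056; +0.9 to +21.4 points) needs no assumed rate, only 50 analysed per arm. SAEs, SADRs and single reaction types are the likeliest to fall in the weak range, because the protocol calls its listed risks rare.

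**What to change.** In Section 14.4.1 and in the Summary's adverse-reaction paragraph:
- Make the between-arm risk difference with its 95% CI (for example the Newcombe score interval) the main comparison for AEs, ADRs, SAEs and SADRs.
- Keep the Chi-square or Fisher p-value as descriptive.
- State that a non-significant result is not evidence of equal safety.

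The cost is a few sentences and one extra table column, with no new data. The downside is a safety statement that looks less favourable, because the intervals will be wide.
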